#### Eligibility criteria

To be eligible, participants need to:Identify as a same-sex attracted woman. This includes transgender women, transgender men, and gender diverse individuals. Transgender men were eligible as these individuals were likely involved in lesbian, bisexual, and queer women’s communities prior to transitioning to male; and if the individual has not undergone gender reassignment surgery, certain female health issues will still affect them.Be aged 18 years or older.Score eight or above on the AUDIT.Own a mobile phone with SMS capabilities and have access to the internet.Respond to both the welcoming email and the test SMS message received after enrolling.

#### Data collection

##### Baseline (T1)

Baseline data are collected using an online survey using *Qualtrics*. The survey primarily measures alcohol use, wellbeing, and current help-seeking. For a list of measures, please refer to Table 1. Participants are asked to provide their primary email address and mobile telephone number to send two follow-up surveys and to deliver the SMS intervention.

**Table 1 Tab1:**
[figure not shown]
SPIRIT Flow Diagram

C = control group; I = intervention group; SE = study entry; AUDIT = the Alcohol Use Disorders Identification Test; PWI-A = the Personal Wellbeing Index – Adult; WHOQOL-BREF = the WHO Quality of Life-BREF; BRS = the Brief Resilience Scale; DASS = the Depression Anxiety Stress Scales; MOS-SS = the Medical Outcomes Study Social Support Survey; TNMS = the Treatment Needs and Motivation Scale

##### Post-intervention (T2)

Following the completion of the four-week intervention, a post-intervention online survey is emailed to participants. Participants in the intervention group are asked to respond to an additional set of questions regarding intervention acceptability. See Table 1 for a list of measures used in the T2 survey.

##### Follow-up (T3)

At 12 weeks post-intervention, all participants will complete a follow-up survey. See Table 1 for a list of measures used in the T3 survey.

#### Random allocation

Individuals are screened for eligibility. The first two eligibility criteria are determined in the baseline survey. If an individual responds that they identify as a man or they are aged under 18 years, they will be automatically directed to the end of the survey. The AUDIT score is calculated by [name] once the baseline survey is received. If the individual scores eight or above, they will then receive a welcome email and test SMS message. Once the receipt of both has been confirmed, participants are randomly allocated into the intervention group or the control group using a computer generated block randomisation at a 1:1 ratio with 10 allocations per block to ensure equal numbers in each group if the recruitment goal is not achieved. The sequence of condition allocations are placed in opaque envelopes with participant identification numbers on the front. Once a participant’s eligibility is determined, an envelope is opened by [name] and the participant is allocated to the experimental condition inside the envelope. As participants are blinded, to reduce bias they will not be informed of the number or frequency of messages in the intervention as this information will reveal which group participants have been randomly allocated to.

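### A single fixed block of 10, with staff-opened envelopes and no staff blinding described, could make up to one allocation in six certain in advance

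*Protocol article*

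**What the plan says.** The section on random allocation fixes one block size, "computer generated block randomisation at a 1:1 ratio with 10 allocations per block". It mentions no variation in size and no stratification. The reason given is "to ensure equal numbers in each group if the recruitment goal is not achieved".

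The concealment device is described as follows: "The sequence of condition allocations are placed in opaque envelopes with participant identification numbers on the front". When a participant qualifies, "an envelope is opened by [name] and the participant is allocated to the experimental condition inside the envelope".

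The steps before that are partly in staff hands. "The AUDIT score is calculated by [name] once the baseline survey is received", and people scoring eight or more are then sent the welcome email and test message. "Once the receipt of both has been confirmed, participants are randomly allocated into the intervention group or the control group". The eligibility criteria make this reply a condition of entry: "Respond to both the welcoming email and the test SMS message received after enrolling".

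The study design section calls the trial single-blind, and the random allocation and discussion sections apply the blinding to participants. No blinding of staff is described.

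**The concern.** An opaque envelope hides the next allocation only if that allocation cannot be worked out from earlier ones. With one list and one constant block size, it sometimes can. Once either arm has its five places in a block, every remaining allocation in the block is fixed.

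The sequence of events matters here. The envelope is opened last, but the step just before it is a confirmation that staff make, and the article states no deadline or reminder rule for it. Someone who already knew the next arm could, deliberately or not, pursue a slow responder more or less keenly, or change the order in which two people are allocated.

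The outcomes are self-reported, and the discussion concedes that participants probably know their arm. Concealment before allocation therefore carries more of the protection against bias than it would in a well-masked trial.

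**Working it through.** **Inputs.** Block of 10, 1:1, so five per arm (random allocation section). Target 50 per group, or 100 in all, which is ten full blocks; 40 completers per group; AUDIT difference 4, SD 6, two-sided 0.05 (power analysis section). The article gives no figure for predictability. Its power figure is reproduced first because it is needed for the cost of the fix.

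**1. Stated power.** With 40 per arm the noncentrality is (4/6) × √(40×40/80) = 2.98 on 78 degrees of freedom. Power is 83.8% by the noncentral t and 84.6% by the normal approximation. The stated 84% is reproduced.

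**2. Certain allocations in a fixed block of 10.** There are C(10,5) = 252 equally likely orderings. At least *r* allocations are forced when the last *r* all belong to one arm, so P(at least *r*) = 2 × C(10−*r*, 5)/252.

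| *r* | orderings with at least *r* forced | exactly *r* |
|---|---|---|
| 1 | 252 | 55.6% |
| 2 | 112 | 27.8% |
| 3 | 42 | 11.9% |
| 4 | 12 | 4.0% |
| 5 | 2 | 0.8% |

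The expected number is (252 + 112 + 42 + 12 + 2)/252 = 420/252 = 1.67 per block. That is 16.7%, or one in six, and 16.7 of 100 participants. In general the share for a block of 2*m* is 1/(*m*+1). Smaller fixed blocks are therefore worse: 20% for 8, 25% for 6, 33% for 4.

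**3. Best guess.** Always naming the arm with more places left (a coin toss when tied) is right 65.3% of the time over the 252 orderings, against 50% with no knowledge.

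**4. How far the one in six can fall.** It assumes that every envelope in a block is opened and that the tally is complete. The envelopes carry participant numbers. If numbers were issued before eligibility was settled (an assumption; the article does not say), some envelopes would stay shut. One unopened envelope per block reduces the share to 0.667/9 = 7.4%, and two reduce it to 0.222/8 = 2.8%.

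**5. Varied block sizes.** I simulated sequences of 100 with an observer who knows all earlier allocations and the set of sizes, but not which size is in use.

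| Scheme | Certain | Best guess right |
|---|---|---|
| Fixed 10 | 16.6% (exact 16.7%) | 65% |
| 6, 10, 14 at random | 1.2% | 65% |
| 4, 6, 8 at random | 2.3% | 68% |

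Varying the size removes nearly all certainty but does not improve guessing. Making the blocks smaller makes guessing easier.

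**6. Balance.** A stop in the middle of a block of 10 can leave the arms 5 apart. That requires stopping at the fifth allocation with all five in one arm, which has probability 2/252 = 0.8% at that stop. Averaged over stopping points the expected gap is about 1.0. With 6, 10 and 14 the worst case is 7 and the average about 1.06. Even a split of 44 and 36 completers (a gap of 8) gives noncentrality (4/6) × √(44×36/80) = 2.97 and power 83.4%, against 83.8% when equal.

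**The case against.** The strongest reply is that little here can be exploited. People enrol themselves through an online survey, the gender and age exclusions are automatic, the AUDIT threshold is a number, and the final step is the participant's own reply. Envelopes are opaque, numbered and opened only after eligibility is settled, which is an accepted procedure. Nothing in the article describes staff chasing or abandoning anyone. This stands, and it confines the exposure to the reply-confirmation step.

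A reader might infer that the study team knows every earlier allocation. The article does not say so. Names are removed, so it cannot be seen whether one person scores the AUDIT, confirms replies and opens envelopes, and a condensed article may leave role separation to the full protocol. Being single-blind concerns knowledge after assignment and does not settle who keeps a tally. What does follow is that whoever opens the envelopes sees their contents.

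A reader might also think that publishing the block size during the study is the problem. It adds little, because participants cannot see earlier allocations.

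Finally, the criticism of the equal-numbers rationale is slight: the expected gap is about one participant, and varied blocks do marginally worse on that aim. Only the word claiming certainty of balance is wrong.

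**Conclusion.** The point holds as a minor design weakness. A single fixed block of 10 with staff-opened envelopes allows up to one allocation in six, at most about 17 of 100, to be known before the last eligibility step is closed.

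This is an upper bound. It rests on someone knowing the block size, seeing all earlier allocations in a single sequence, keeping count, and every envelope being used. With one or two unopened envelopes per block it falls to 7.4% or 2.8%.

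The article does not support a claim that selection occurred, and it offers no basis for sizing any bias in the outcomes. The case for change is that a better method is available at almost no cost, not that the results are compromised.

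**What to change.** For any participants still to be allocated:

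- Generate the remaining list with randomly varying, undisclosed block sizes, for example 6, 10 and 14.
- Hold that list where enrolling staff cannot see it, and release each allocation only after both confirmations are time-stamped and eligibility is locked. This step matters because varied blocks alone leave best-guess accuracy near 65%.
- Reword the rationale quoted above ("to ensure equal numbers in each group if the recruitment goal is not achieved") to say that blocking keeps numbers approximately equal.

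Existing allocations stand. The cost is a new list and a small set-up change, with no extra participants. The worst-case mid-block gap rises from 5 to 7, which costs well under one percentage point of power.

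The participant recruitment section says that data collection, not recruitment, is ongoing, so allocation may already be complete. In that case, state in the trial report that the block size was fixed at 10, say who knew earlier allocations and who confirmed the replies, and list this as a limitation.

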#### Intervention group

The intervention consists of automated culturally tailored supportive SMS messages which are delivered through *MessageMedia*, an Australian SMS platform. It is designed to begin on a Monday and end on a Sunday. Messages are delivered daily for four weeks with two messages on Thursdays, Fridays and Saturdays, as people typically drink alcohol on these days (40 messages in total). Messages are sent at varying times between 3:00 p.m. and 4:30 p.m., and on days with two messages, the second is delivered between 6:00 p.m. and 8:00 p.m. On Sundays, the message asks participants to reply via SMS with the number of standard drinks they have consumed in the past seven days. In the welcome email, all intervention participants receive a standard drinks chart and an author-developed list of LGBT specific or friendly alcohol and mental health services.

##### Intervention development

The intervention was co-designed with potential consumers and utilised an Intervention Mapping framework [22, 23] which provides a best practice process to intervention development with a strong focus of engaging potential consumers in the developmental process. This consisted of six steps to develop an evidence-based intervention with each step being cumulative so that the result of each step guided the next ([name], [name], [name], [name], & [name]: Development of a tailored SMS alcohol intervention for same-sex attracted women using an intervention mapping framework, in preparation).

The first step involved a needs assessment to identify the gap in culturally tailored or appropriate alcohol treatment services available to SSAW. This included a comprehensive literature review and running focus groups with SSAW to explore whether they wanted a culturally tailored service and what they believed should be included. Step two involved developing a table of performance objectives (see Table 2) in which each cell of the table outlined what participants would need to learn or change in order to reduce their alcohol intake, improve their wellbeing, and increase their access to alcohol support services. The selection of these three primary outcomes was influenced by the literature and focus group discussions. Alcohol reduction was selected because research has consistently demonstrated a greater risk for hazardous alcohol use among SSAW compared to heterosexual women [3, 4, 24]. Wellbeing was selected as SSAW who drink hazardously also tend to have a lower level of general wellbeing as they commonly report experiences of sexual and physical abuse [25, 26], low social support [27, 28], and less access to housing, employment and healthcare [29–31]. Finally, help-seeking was selected as SSAW are typically reluctant to seek professional help due to a lack of services which are responsive to their unique needs [5, 8].

**Table 2 Tab2:** Table of Performance Objectives

Performance Objectives	Targets of Change			
	Resilience	Mental Health	Social Support	Motivation to Change
Reduce alcohol intake	Able to cope with general and sexual orientation related stress and adversity in a healthy way rather than using alcohol as a coping mechanism.	Able to use healthier coping strategies to deal with psychological distress related to sexual orientation rather than using alcohol to self-medicate.	Make social connections where alcohol is not the focus of social gatherings.	Understand what can be gained by reducing alcohol intake, feels confident about the ability to successfully reduce intake, and makes it a priority to achieve this.
Improve wellbeing	Able to approach challenges with confidence, realistic optimism, and a sense of control.	Is aware of own potential and limits, and can cope with stress and challenges.	Increase time with positive social network who evoke self-confidence and optimism.	Understand what can be gained by being healthier, feels confident about ability to successfully make these changes, and will prioritise looking after health and well-being.
Increase help-seeking	Understand that by receiving positive support and help, aspects of resilience such as self-efficacy, hope, and coping, will be strengthened.	Is aware of general and SSAW sensitive mental health services and understand what can be gained by seeking support.	Is aware that informal supports (e.g. peers and support groups) can be positive sources of help and support but also understand that formal sources are important for significant emotional and mental health issues.	Is aware of the services that are available to SSAW, feels confident in ability to engage with the services, and will make it a priority to contact services for help and support.

Four mediating variables were included in the table of performance objectives (see Table 2). These were identified during the needs assessment and were deemed important for successful behaviour change among SSAW. Improving resilience was the first mediator identified and was selected because the main elements of resiliency, such as self-efficacy, hope, and coping [32], have the potential to help individuals cope with stress and adversity in a healthy way [33]. The second mediator, mental health, was deemed to be an influential factor in SSAW’s ability to improve the primary outcomes as they have been found to experience higher levels of depression and anxiety compared to heterosexual women [34], and SSAW who have poor mental health have been found to drink at hazardous levels [24, 35]. Facilitating social support was chosen as the third mediator because individuals who lack social support are more vulnerable to poor health outcomes [36]. Lastly, enhancing motivation to change was deemed an important factor as it can influence an individual’s desire to comply with and finish a treatment program [37].

Step three in the Intervention Mapping framework involved selecting behaviour change techniques which were operationalised in step four. The selection of behaviour change techniques was guided using three theoretical frameworks: the Information-Motivation-Behavioural Skills model [38], the Health Belief Model [39, 40], and the Theory of Planned Behaviour [41]. SSAW were consulted during step four which involved developing the SMS statements in order to receive their input on the messages to ensure the language and content was appropriate and perceived to be helpful. Table 3 displays some example SMS messages that were delivered to the intervention group. The current paper describes the process for implementing steps five and six which pertain to the delivery and evaluation of the intervention.

**Table 3 Tab3:** Example SMS Messages Delivered to the Intervention Group

Target	Message Statements
Performance objective: Reduce alcohol intake	
Resilience	• Identify and write down triggers that make you want to drink. These may include social (ie discrimination, others drinking) or health (ie distress) factors.
Mental health	• It’s common to use alcohol to cope with distress related to discrimination. Write down some healthier ways to cope with distress, ie deep breathing, exercise.
Social support	• Does your partner/housemate drink? Try to reduce your drinking together. You can support each other and both stick to your goals when at a bar or pub.
Motivation to change	• What is your alcohol reduction goal? When and how will you start? Eg, Not to exceed 2 drinks when I’m out, starting on Saturday night.
Performance objective: Improve well-being	
Resilience	• Does visiting a new doctor make you feel distressed? Write down ways you can confidently approach this. Also try visiting doclist.com.au for a list of services.
Mental health	• LBQ+ women face everyday stress plus sexual orientation related stress and sexism. If you’re having a hard day, know your limits and give yourself a break.
Social support	• If you encounter discrimination, homophobia, abuse, try talking to someone who makes you feel good about yourself, ie your partner, a family member, or friend.
Motivation to change	• Health includes physical, mental and social aspects. Think of how/when you can improve these areas ie go walking with a friend on Saturdays.
Performance objective: Increase help-seeking	
Resilience	• Seeking support can help you identify or relearn healthy coping strategies. Visit or call QLife for support and referrals: qlife.org.au/support/ or [name]
Mental health	• If you are feeling stressed/anxious/down etc. set aside a time in your calendar to make an appointment with someone who can help.
Social support	• Connecting with like-minded people is important. Support groups are a great addition to formal support as you will meet others who get what you’re experiencing.
Motivation to change	• Are bad past experiences stopping you from seeking support? Refer to the list of services that was emailed to you for LBQ+ women appropriate services.

#### Comparator group

Consistent with other trials that have delivered SMS alcohol interventions (e.g. [15, 42]), participants in the control group receive a generic weekly message: “Thank you for participating in this study. For LGBT specific information on drug/alcohol use, mental health and sexual health, visit http://touchbase.org.au”. These participants do not receive a standard drinks chart or a list of support services. At the end of the study, after completing the 12-week follow-up survey, participants receive the list of support services and are offered the chance to receive the intervention messages.

### Measures

#### Demographic information

The baseline survey includes: standard demographic questions, such as age, residential location and education; questions related to sexuality ask participants about their sexual identity, behaviour and attraction; questions related to gender identity asking whether they identify as female, transgender female, transgender male, non-binary, or another identity not listed; and questions related to relationship status, whether participants are currently in a relationship, with how many people, and the gender of their partner/s.

#### Alcohol use and severity

Severity of alcohol use is measured using a modified version of the AUDIT, a screening tool developed by the World Health Organisation [43]. The instrument includes ten questions answered on Likert scales assessing three domains: hazardous alcohol use, dependence symptoms, and harmful alcohol use. Questions three to 10 were changed to ask participants about drinking outcomes in the past four weeks at T2 and past 12 weeks at T3 rather than the past year to avoid collecting overlapping data. A score of 0–7 indicates ‘low-risk’ alcohol use; a score of 8–15 indicates a ‘hazardous level’ of alcohol use; a score of 16–19 indicates a ‘harmful level’ of alcohol use; and a score of 20 or more indicates ‘high-risk’ alcohol use. This scale has been validated and successfully used in different populations [43, 44].

Alcohol use is measured by asking participants to report the number of standard drinks they consumed in the previous 30 days. A basic standard drinks chart is included to assist with calculations.

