**Methods:**

A randomised controlled trial comparing a culturally tailored SMS intervention (The Step One Program) with a generic ‘thank you’ message, and a nested qualitative study to further explore the intervention’s feasibility and acceptability. The Step One Program was co-designed using an Intervention Mapping framework and engaging potential consumers in the developmental process. Participants are block randomised (1:1 ratio) and followed up at the completion of the intervention and at 12 weeks post-intervention. The primary outcomes are alcohol reduction (as measured by the Alcohol Use Disorders Identification Test and self-reported alcohol intake), wellbeing (as measured by the Personal Wellbeing Index – Adult), and help-seeking (as measured by the number of alcohol services accessed and frequency of access). Upon completion of the 12-week post-intervention survey, participants in the intervention group were contacted via email regarding a phone interview on intervention acceptability.

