### Data analysis

All data will be de-identified and coded to ensure participant anonymity and it will stored securely on a password protected computer. Participant names, corresponding identification numbers, and contact information will be kept in a separate password protected file on a secure computer at Deakin University. Only the research team will have access to secured information. Only the de-identified data will be used in the analysis phase and in the summary of main outcomes that will be delivered to participants, any subsequent publications, and conference presentations. A data monitoring committee is not needed for this study as it is a non-therapeutic (behavioural) trial using low-risk procedures, and as such, the study team will be monitoring the data.

Analyses will be conducted using an intention-to-treat (ITT) approach [59], with all randomised participants analysed in their allocated group regardless of the intervention uptake. Every effort will be made to minimise missing data and where appropriate, multiple imputation will be used to handle missing data.

Baseline participant’s characteristics will be compared between the intervention and control group using Chi-squared or Fisher’s exact test for categorical variables, and *t* test or Kruskal-Wallis test for numerical variables. Drop-out bias will also be assessed using the same approach but comparing the baseline characteristics of participants with complete data against those lost to follow-up as a function of treatment group.

The intervention effect during the 12-week follow-up on numerical outcomes will be assessed using linear mixed models including group, time (T1, T2 and T3) and group by time interaction as fixed effects and participant as a random effect.

The feasibility of the Step One Program will be determined by the proportion of individuals who completed the baseline survey and were eligible to participate, how often participants read the SMS messages, how often they respond to Sunday SMS messages, and completion of follow-up surveys. Intervention acceptability will be reported by 1) summarising the multiple choice responses to the intervention acceptability questions in the T2 survey, and 2) performing qualitative analysis of the short answer responses and interviews using simple coding to identify recurring patterns and themes.

We will explore whether changes between T1 and T2 in the primary outcomes are correlated with changes in the potential mediator variables.

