### Power analysis

The target sample size is 50 participants per group. Assuming 20% attrition rate, we estimate to collect complete data from 40 participants in each group. Sample size calculations are based on the only available Australian study of alcohol consumption in this population, the Australian Alcohol and lesbian/bisexual women – insights into culture and emotions (ALICE) study [1], which provides estimates for the AUDIT score. A sample size of 40 participants per group has 84% power for detecting a post-intervention mean change of 4 points in the AUDIT score, when the standard deviation is assumed as 6 for two independent groups, two-tailed test, and significance level 0.05. This sample size will achieve 80% power to detect effect sizes larger than 0.63 for any of the other scores outcomes.

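### AUDIT questions 3 to 10 cover a different recall window at each visit, so AUDIT change over time cannot be read as change in drinking; the between-arm comparison survives but should use T1 AUDIT as a covariate

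*Protocol article*

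**What the plan says.** All of this is in the protocol article.

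- **Outcome.** The abstract's Methods paragraph lists among the primary outcomes "alcohol reduction (as measured by the Alcohol Use Disorders Identification Test and self-reported alcohol intake".
- **Instrument.** Under Alcohol use and severity: "The instrument includes ten questions answered on Likert scales assessing three domains". The window is then altered for eight of the ten: "Questions three to 10 were changed to ask participants about drinking outcomes in the past four weeks at T2 and past 12 weeks at T3". The same sentence sets these windows against the past year and gives the reason: "in the past four weeks at T2 and past 12 weeks at T3 rather than the past year to avoid collecting overlapping data". T1 is therefore the past-year form, by implication rather than by direct statement. The separate 30-day standard-drinks question in the same section is described with one window.
- **Model.** Data analysis assesses numerical outcomes with "linear mixed models including group, time (T1, T2 and T3) and group by time interaction as fixed effects and participant as a random effect". It makes no allowance for the changed window.
- **Mediators.** The same section adds: "We will explore whether changes between T1 and T2 in the primary outcomes are correlated with changes in the potential mediator variables".
- **Planning figures.** Power analysis takes its AUDIT figures from an earlier Australian survey "which provides estimates for the AUDIT score". It plans on a 4-point difference and an SD of 6, and does not mention the shorter windows.
- **Hypotheses.** These compare the two arms, at the end of the 4-week intervention and 12 weeks later.

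**The concern.** A score that asks about a year, then a month, then a quarter is not the same measurement three times. Someone whose drinking is constant has less time at T2 in which to have experienced any given harm or dependence symptom, and more again at T3. A common fall followed by a partial return could then be built into the instrument.

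Three kinds of statement would be at risk. First, an apparent improvement in both arms: the Discussion already anticipates that controls may improve, citing a trial of an online programme in which everyone drank less, and a window artefact would look the same. Second, any reading of T2 against T3 as persistence or relapse. Third, the mediator exploration, where the AUDIT change score would mix real change with a mechanical component.

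**Working it through.** **1. The plan's own figures.** Inputs from Power analysis: 40 analysed per arm, difference 4, SD 6, two-sided 0.05.
- Standard error = 6 × √(2/40) = 1.342, and 4/1.342 = 2.98.
- Power is 84.6% by the normal approximation and 83.8% by the noncentral t with 78 df. The stated 84% reproduces.
- 40/(1 − 0.20) = 50 per arm.
- Detectable effect at 80% power = (1.960 + 0.842) × √(2/40) = 0.63.

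There is no arithmetic error.

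**2. The windows.** Taking a year as 52 weeks, the T1 window is 52/4 = 13 times the T2 window, and the T3 window is 12/4 = 3 times the T2 window. This affects 8 of 10 questions.

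**3. Size of a spurious time effect.** The documents give no item-level data, so this is an assumption with a range. Suppose questions 3 to 10 contribute 10 of a mean total of 15 at T1, drinking does not change, and the shorter windows multiply that part by f. The apparent change is −10 × (1 − f).

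| f at T2, T3 | T1 to T2 | T1 to T3 | T2 to T3 |
|---|---|---|---|
| 1, 1 | 0 | 0 | 0 |
| 0.8, 0.9 | −2.0 | −1.0 | +1.0 |
| 0.6, 0.8 | −4.0 | −2.0 | +2.0 |

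The last row matches the planned 4-point difference, with no change in drinking.

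**4. Between-arm comparison.** A simulation on the same assumptions (40 per arm, T1 SD about 5.6, 4,000 repetitions) gave these results.
- No treatment effect: the difference between arms in T1-to-T2 change was 0 to within 0.02, and the T2 comparison rejected in 4.9% to 5.4% of runs.
- True 4-point effect, with 70% of it in questions 3 to 10: the T2 difference reads as 1.2 + 2.8 × 0.8 = 3.4 or 1.2 + 2.8 × 0.6 = 2.9. The T2 SD fell to 4.8 or 4.0, and power was 88% to 89% with or without shrinkage.
- At T3 the same constant effect would read as 1.2 + 2.8 × 0.9 = 3.7 or 1.2 + 2.8 × 0.8 = 3.4. An unchanged effect would seem to grow from T2 to T3.

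**5. Precision of a change contrast.** With complete data, the T1-to-T2 interaction contrast is the difference in mean change, so T1 is subtracted with weight 1. Per-person variance is s1² + s2² − 2ρ·s1·s2. With T1 as covariate it is about s2²(1 − ρ²). Take s1 = 6; s2 and ρ are assumed.

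| ρ | s2 | Change | Covariate | Ratio |
|---|---|---|---|---|
| 0.7 | 6 | 21.6 | 18.36 | 1.18 |
| 0.7 | 5 | 19.0 | 12.75 | 1.49 |
| 0.7 | 4 | 18.4 | 8.16 | 2.25 |
| 0.5 | 6 | 36.0 | 27.0 | 1.33 |
| 0.5 | 5 | 31.0 | 18.75 | 1.65 |
| 0.5 | 4 | 28.0 | 12.0 | 2.33 |

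The more the T2 scale is compressed, the more weight-1 subtraction costs. At s2 = 4 the change contrast (18.4 or 28.0) is less precise than ignoring baseline altogether (16).

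**6. Mediator exploration.** Under step 3 the mechanical fall is (1 − f) times a person's own T1 score on questions 3 to 10. At f = 0.6, a score of 5 falls by 2 and a score of 20 falls by 8. AUDIT change then partly encodes baseline severity, and because the correlation runs across participants, having the same window in both arms does not remove this.

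**The case against.** The strongest reply is that the planned test is sound. The hypotheses are between-arm, both arms answer the same form at each visit, and a common shift goes into the time main effect, about which nothing is hypothesised. This stands. A reader might infer that the randomised AUDIT comparison is biased; step 4 shows that it is not under no effect.

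Shortening the window was also deliberate and reasonable. A past-year question at T2 would cover about 48 of 52 weeks before the intervention. The point is not to restore the past-year form but to stop treating the forms as interchangeable.

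Other stronger readings are also unsupported:

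- **Lost power.** Compression may shrink the SD along with the difference: 3 points with SD 4.5 keeps about 84%. Power falls only if the difference shrinks more than the SD (3 points at SD 6 gives 59.8%). The documents show neither outcome, nor the recall window behind the survey's estimates.
- **Risk bands misapplied.** The section describes the bands, but the only cut-off put to use is at entry: "Score eight or above on the AUDIT". No band analysis is planned at T2 or T3.
- **A certain fall and rebound.** An event occurring 3 times a year would be reported at least once by 95% over a year, 21% over 4 weeks and 50% over 12 weeks. That is a selected case. A monthly event gives about 60% at 4 weeks and 94% at 12; a weekly one gives 98% and nearly 100%. The article gives no response options, and an item scored as a rate need not fall at all. The right word is may.
- **Equal variance across visits.** A participant random effect does not settle the residual structure, which an article can leave to the analysis plan.

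Finally, the mediator analysis is exploratory, and the other primary outcomes in it are untouched by the AUDIT windows.

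**Conclusion.** The concern holds in a limited form. The article fixes two things that do not fit together: a recall window that differs by visit for eight of ten AUDIT questions, and analyses that treat T1, T2 and T3 as the same outcome. As written, the AUDIT time effect, within-arm AUDIT change, T2-to-T3 comparisons (including of the size of the treatment effect) and AUDIT's part of the mediator exploration cannot be interpreted as change in drinking.

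The size is unknown. The 2- to 4-point spurious fall at T2 rests on assumed shrinkage of 0.8 to 0.6 and an assumed 10-point contribution from questions 3 to 10. The between-arm comparison at each visit remains valid under no effect. Its cost is possible imprecision if the effect is read from a change contrast: a variance ratio of 1.18 to 2.33 over the assumed SDs and correlations, of which 1.18 to 1.33 would arise even with equal SDs. The 84% power is arithmetically right; whether 4 points and SD 6 suit the shorter windows cannot be judged from the documents.

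**What to change.** 1. Compare arms on AUDIT at T2 and at T3 with T1 AUDIT as a covariate, not as a level of the outcome. One mixed model on T2 and T3 with T1 as covariate would serve. Participants with T1 only would then enter through the multiple imputation that Data analysis already mentions; say so.
2. State the T1 window explicitly, and state that within-arm AUDIT change and T2-to-T3 AUDIT differences will not be interpreted.
3. Base change over time, and the alcohol part of the mediator exploration, on the 30-day standard-drinks measure. This removes the window artefact only. Entry requires a baseline AUDIT of 8 or more, so regression to the mean can still affect within-arm change.
4. Note in Power analysis that the 4-point difference and SD of 6 were not shown to apply to the 4-week and 12-week forms.

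The cost is a few sentences and one change of model for one outcome, with no new data. The article reports data collection as ongoing, so this can be settled before analysis. What is given up is any statement about AUDIT change within an arm.
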